**Figure 2 F2:**
[figure not shown]
SUSPEND trial processes.

#### Subject withdrawal

Participants will remain on the trial unless they chose to withdraw consent or the principle investigator, chief investigator or trial manager feels it is no longer appropriate for the participant to continue (for example, the participant becomes unable to complete the trial documentation). Once the participant has been withdrawn from the trial, participant questionnaires will not be collected; however, permission will be sought for the research team to continue to collect outcome data from the participant’s hospital notes (using the case report forms).

In the event that participants are withdrawn from the study medication for any reason (for example, a serious adverse reaction or event occurs), they will still continue in the trial and will be asked to complete the trial documents.

### Trial medications

#### Investigational medicinal products

Tamsulosin hydrochloride (Petyme) will be sourced by Tayside Pharmaceuticals from Teva UK in the form of 400 μg modified release capsules.

Nifedipine (Coracten) will be sourced by Tayside Pharmaceuticals from UCB Pharma in the form of 30 mg sustained release capsules.

The placebo will be manufactured by Tayside Pharmaceuticals.

The medicinal products will be over-encapsulated to maintain the blinding of the trial. Trial medication will be presented as capsules in amber glass containers with a childproof closure and labelled according to Annex 13 of Volume 4 of *The Rule Governing Medicinal Products in the EU: Good Manufacturing Practices*[21].

The medicinal products and the placebo will be over-encapsulated, packaged and labelled by Tayside Pharmaceuticals according to good manufacturing practice.

#### Dosing regimen

Participants will take one capsule of the trial medication per day until stone passage occurs or for a maximum of 28 days.

#### Drug accountability

Blinded treatment packs will be stored by the local pharmacy according to manufacturer’s instructions until dispensed to the participant. Detailed dispensing records will be kept by the pharmacy.

#### Subject compliance

Upon randomization, each participant will be assigned a unique participant numbered pack of blinded medication. Participants will be instructed to store the medication according to the manufacturer’s instructions. Participants will be asked to record whether they completed the full course of treatment in the 4-week questionnaire. Unused medication or empty packaging should be returned by the participant at the 4-week follow-up visit and returned to the pharmacy. Participants who do not attend the 4-week visit will be instructed to destroy the medication. Participants will also be treated with the usual standard of care at the treating establishment, including prescribed analgesia.

#### Concomitant medications

Patients currently taking rifampicin or digoxin are excluded from the trial. Potential interactions are taken from the summary of product characteristics for each product; the participant’s GP will also receive this information.

### Outcome measures

The trial has a primary clinical and a primary economic outcome, reflecting the multidimensional nature of the possible effects the intervention may have.

#### Primary

• Clinical: the primary outcome is spontaneous passage of ureteric stones at 4 weeks (defined as no further intervention required to facilitate stone passage).

• Economic: a reduction in incremental cost per quality-adjusted life years (QALYs) gained at 12 weeks. The calculation of QALYs will be based on the participants’ responses to the EQ5D.

#### Secondary

• Patient-reported: a reduction in the severity of pain as measured by a numeric rating scale [22,23]. Generic health profile will be measured by the SF 36 and the use of analgesia.

• Clinical: time to passage of stone; further interventions received at 12 weeks.

• Safety: participant-reported discontinuation of trial medications.

• Economic: NHS primary and secondary care use and costs up to three months, incremental cost per surgical interventions averted; modelled incremental cost per QALY beyond the 12-week trial follow-up.

#### Timing and measurement of outcome assessment

Outcomes will be assessed at 4 weeks and 12 weeks post randomization, as shown in Table 1.

**Table 1 T1:** Source and timing of measures

**Outcome measures**	**Source**	**Timing**		
		**Recruitment**	**Post randomization**	
			**4 weeks**	**12 weeks**
Need for additional intervention	Case report form		×	×
Additional interventions received	Participant questionnaire and case report form		×	×
Pain (numeric rating scale)	Participant questionnaire	×	×	
Health profile and status (SF36, EQ5D)	Participant questionnaire	×	×	×
Use of analgesics	Participant questionnaire		×	
Adverse events	Participant questionnaire		×	×
Time to passage of stone	Participant questionnaire and case report form		×	×
NHS primary and secondary healthcare use	Participant questionnaire and case report form			×
Participant out of pocket costs	Participant questionnaire			×

EQ5D, European Quality of Life, 5 Dimensions; SF36, Short Form (36) Health Survey.

### Safety

#### Timing and recording of safety parameters

Information regarding participant discontinuation of medication due to adverse events will be collected at 4 weeks in the participant questionnaire.

#### Procedures for recording and reporting adverse events

##### Adverse events that will not be reported

Non-serious events will not be collected or reported. Planned hospital visits for conditions other than those associated with the ureteric stone will not be collected or reported. Hospital admissions (planned or unplanned) associated with the treatment of the ureteric stone diagnosed at the time of entry to the trial are expected. These will be recorded as an outcome measure, but will not be recorded or reported as serious adverse events.

##### Procedure for adverse event recording in this trial

All adverse events will be assessed in respect of severity (serious or not), relationship to trial medication (suspected or not suspected), whether expected or unexpected, duration and, therefore, whether constituting a serious adverse event, by the local principle investigator or chief investigator, or their deputies.

Participants will be advised to contact their GPs should they experience an adverse event between the period following treatment and the 12-week follow-up questionnaire. This is current clinical practice for participants receiving tamsulosin or nifedipine within the NHS. When notified of trial participation, GPs will be asked to notify the trial office of any serious adverse reactions or events (for example, unexpected admission to hospital) in a timely manner. This will provide a robust system for the notification of any serious adverse reactions or serious adverse events (both expected and unexpected) occurring outside the trial visit.

1. Non-serious adverse events will not be collected. Participants will be asked whether they discontinued the study medication due to adverse reactions in the 4-week questionnaire.

2. All confirmed serious adverse events are to be notified to the co-sponsors and chief investigator as soon as the investigator or trial office (via a GP) becomes aware, either orally or in writing, of the event, and this should be followed by a written report on the event.

### Adverse reaction and unexpected adverse reaction reporting

#### Fatal or life-threatening suspected unexpected serious adverse reactions (SUSARs)

The chief investigator (or his designee) or co-sponsor will forward reports on fatal or life-threatening suspected unexpected serious adverse reactions (SUSARs) (that is, serious unexpected adverse events where a causal link between the drug and the event is suspected) to the Medicines and Healthcare Regulatory Authority (MHRA) and the research ethics committee within 7 days of their first knowledge of the minimum criteria using the relevant proforma. A copy will also be sent to the co-sponsor, the manufacturer and the data-monitoring committee. Follow-up information will be forwarded to the MHRA and ethics committee within 8 days.

#### Non-fatal and non-life-threatening SUSARs

The chief investigator (or designee) or co-sponsor will forward reports on non-fatal and non-life-threatening SUSARs to the MHRA and the research ethics committee within 15 days of their first knowledge of the minimum criteria using the relevant proforma. A copy will be sent to the co-sponsors, the manufacturer and the data-monitoring committee. Follow-up information will be forwarded to the MHRA and ethics committee within 8 days.

#### All other serious adverse reactions

The trial office, with the assistance of the chief investigator, will prepare a summary of all serious adverse reactions every six months. These will be distributed to the participating investigators, co-sponsors, manufacturer, trial steering committee and data-monitoring committee.

In addition, all suspected serious adverse reactions will be collated annually and submitted to theresearch ethics committee and the MHRA, in accordance with the guidance on annual safety reporting.

The data-monitoring committee will regularly assess the safety data collected for the trial and will have the ability to advise that the trial is temporarily or permanently halted based on safety concerns, according to the criteria defined in their charter.

#### Pregnancies

Pregnancy is not regarded as a serious adverse event, but will be recorded and reported. Pregnancy will be prevented as far as is practicable, but in the event a woman does become pregnant on the trial, she will be followed throughout her pregnancy and any serious adverse events at delivery will be recorded and reported. If necessary, the development of the newborn will be monitored for an appropriate period after delivery.

#### Sample size

The combined data from the two recent meta-analyses [17,18] suggest a relative risk of approximately 1.50, comparing MET (either α-blocker or calcium-channel blocker) against ‘standard care’ on the primary outcome. These reviews indicate a spontaneous stone passage rate of approximately 50% in control groups in the included randomized controlled trials. Only three of the included randomized controlled trials directly compared a calcium-channel blocker with an α-blocker, and these suggested that α-blockers are likely to be superior to calcium-channel blockers. Combining information from Singh [18] and Hollingsworth [17], stone passage rates for the α-blocker and calcium-channel blocker groups were approximately 85% and 75%, respectively. The most conservative sample size is required to detect superiority between the two active treatments and to this end will power the trial. To detect an increase of 10% in the primary outcome (spontaneous stone passage) from 75% in the calcium-channel blocker group to 85% in the α-blocker group, with type I error rate of 5% and 90% power, requires 354 per group; adjusting for 10% loss to follow-up inflates this to 400 per group. Since all treatment comparisons are pre-specified, no adjustment for multiplicity has been made [24]. Recruiting 1,200 participants (randomizing 400 to each of the three treatment groups; α-blocker, calcium-channel blocker and placebo) would provide sufficient power (>90%) for all other comparisons of interest.

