Two recent meta-analyses have reported the potential role of α-blockers and calcium-channel blockers in MET. Hollingsworth and co-workers [17] included nine randomized controlled trials, which included 693 subjects, although all but one trial had serious methodological flaws. Studied interventions included the calcium-channel blocker nifedipine and several different α-blockers whilst the comparative control arms included placebo, other vasodilators, antispasmolytics, anticholinergic therapy and corticosteroids. Overall spontaneous stone passage occurred in 47% of the control group whilst patients given MET with either drug were 65% more likely to pass the stone, with an absolute risk reduction of 31%. Three studies reported a head-to-head comparison between nifedipine and α-blockers. Two of these studies did not report any statistically significant difference in stone passage rates between the two drugs, whilst one study found the α-blocker to be superior to nifedipine, with a relative risk reduction of 26%.

In a more recent systematic review and meta-analysis, Singh and colleagues [18] included 22 studies; of which 13 assessed α-blockers, 6 assessed nifedipine, and 3 assessed both drugs against control. In the pooled analysis of 16 studies using α-blockers (*n* = 1,235), those receiving active treatment were 59% more likely to pass the stone, with a baseline stone passage rate of 50% in the control group. The incidence of mild adverse effects was 4%. The corresponding pooled result for nifedipine (nine studies, *n* = 686) showed that active treatment gave a 50% increased likelihood of stone passage, with an absolute risk reduction of 26%. The incidence of mild adverse effects was 15%. Both drugs significantly shortened, by between 2 and 6 days, the average time to stone expulsion [18]. However, the overall quality of the trials was poor.

In both meta-analyses, the majority of studies involved stones <10 mm located in the lower (distal) ureter. These two reviews both concluded that a large, high-quality randomized controlled trial is required to confirm their findings, suggesting that MET with either drug class can enhance spontaneous stone passage rate. In addition, several studies have previously reported that MET can significantly reduce the pain burden among patients in terms of reducing the frequency of pain episodes, pain severity and analgesic requirements.

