However, more recent results provided by Bensalah and co-workers [19] appear to challenge the notion that α-blockers enhance spontaneous ureteric stone passage. The study, recently presented as an abstract, was a prospective, multicentre, randomized, double-blind, placebo-controlled trial, which evaluated the efficacy of tamsulosin versus placebo in patients with ureteric colic caused by distal ureteric stones. A total of 129 patients were treated for 42 days or until stone expulsion. At 42 days, there was no significant difference between the spontaneous expulsion rates between placebo (70.5%) and tamsulosin (77.0%; *P* = 0.41), nor in the mean stone passage times (10.1 and 9.6 days, respectively). Nevertheless, the overall mean stone diameter was 3.1 mm, which is smaller than all of the earlier studies included in the meta-analyses by Hollingsworth [17] and Singh [18]. The spontaneous stone passage rate in the placebo arm was high (70.5%) in comparison with other studies included in the two meta-analyses.

There is limited evidence on the cost-effectiveness of MET; an indirect cost-benefit analysis based on cost data from the USA and four European countries suggested that the use of tamsulosin could potentially result in a cost saving of US$ 1,132 per patient episode over conventional ‘watchful waiting’ [20].

In summary, the role of MET in reducing the morbidity and economic costs associated with ureteric stone disease is promising. The majority of clinical trials conducted to date have been small and of poor to moderate quality in terms of trial methodology or design. Furthermore, they have lacked a comprehensive economic evaluation. There is thus an urgent need for a definitive randomized controlled trial, such as that described in this protocol to inform the clinical management of patients with ureteric stone disease.

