## Discussion

The main practical challenge of this trial has been the identification and recruitment of participants, owing to the nature of ureteric stone disease and the care pathway for these patients within the NHS. The majority of patients present to secondary care units via emergency departments, often out of normal hours, and this is problematic for site research staff, as there is no way of predicting how, where and when these patients might seek treatment. The availability of the clinical trial pharmacist (often only during normal office hours) to dispense trial medication has also had implications for recruitment. In some cases, participants have volunteered to come back and collect trial medication during pharmacy hours, but there have been occasions where they have not complied with this requirement.

As the trial has progressed, we have seen a lower than expected response rate to the participant questionnaires. Strategies to improve response rate have been employed, including text-message pre-notification of questionnaire delivery, email delivery of reminder questionnaires, short- form questionnaires at 12 weeks (capturing the EQ5D data only) and monetary incentives (unconditional £5 gift voucher for UK high street stores) sent with the 12-week questionnaires. The impact of these will be discussed in the full trial report.

Our choice of primary outcome measure, where stone passage is defined as no further intervention required, is a pragmatic one and encompasses patient (symptoms), clinical (continued presence of stone), and healthcare delivery aspects of stone treatment. Although previous triallists have recorded stone-free rate as confirmed by imaging techniques (for example, CTKUB, plain X-ray of the kidney, ureter and bladder), we considered that participants would not receive imaging as part of their standard care in the NHS and that there are safety concerns with asking them to undergo such procedures purely to fulfil the requirements of the trial. Additionally, stone-free rate confirmed by imaging does not allow for a cost-effectiveness assessment, which will be key to evaluating the effect of MET. Any possible centre and other biases relating to outcome attribution and recording should be mitigated by blinding of the participants and healthcare professionals, randomization and the high sample size of the trial.

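### The 85% α-blocker passage rate that sizes the trial does not follow from the review figures the protocol quotes, which imply a tamsulosin–nifedipine gap of about 4.5 to 4.7 points rather than 10

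*Protocol article*

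**What the plan says.** The Sample size section takes a control passage rate of about 50% and a relative risk of about 1.50 for medical expulsive therapy (MET) from two meta-analyses. It then says that, on combining the two, "stone passage rates for the α-blocker and calcium-channel blocker groups were approximately 85% and 75%, respectively". The tamsulosin–nifedipine comparison is chosen to size the trial: 75% v 85% "with type I error rate of 5% and 90% power, requires 354 per group", and "adjusting for 10% loss to follow-up inflates this to 400 per group". For everything else, 1,200 participants "would provide sufficient power (>90%) for all other comparisons of interest".

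The Background section reports what the same two reviews found:

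- Later review, α-blockers (16 studies): "those receiving active treatment were 59% more likely to pass the stone, with a baseline stone passage rate of 50% in the control group".
- Later review, nifedipine (nine studies): "active treatment gave a 50% increased likelihood of stone passage, with an absolute risk reduction of 26" per cent. Read as a gain in passage, this is +26 points.
- Earlier review, either drug: 47% passage in controls, 65% more likely to pass on treatment, an absolute difference of 31 points. The result is not split by drug.
- Three head-to-head trials in the earlier review: two without a significant difference, and one favouring the α-blocker with a relative reduction of 26%.

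Hypothesis 2, at the end of the Background section, separately sets a 10-point advantage of tamsulosin over nifedipine as the effect under test.

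**The concern.** The protocol prints both the review figures and the rates said to come from them, and for the α-blocker they disagree. The sample size is driven by the difference between the two active arms, so a shift of about 5 points in one rate roughly halves the effect being sized for.

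Two things are at stake. First, a reader is told that a 10-point difference is what the literature shows, when the quoted pooled results point to less than half of that. Second, if the true difference is near the quoted pooled evidence, the comparison that sets the sample size would more likely miss it than find it. A null result would then be easy to over-read.

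**Working it through.** **1. Reproduce the plan's figure.** Inputs from the Sample size section: p₁ = 0.75, p₂ = 0.85, type I error 5%, power 90%. Sidedness is not stated; two-sided is assumed because it reproduces the plan's number.

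n = [1.96·√(2·p̄(1−p̄)) + 1.2816·√(p₁(1−p₁) + p₂(1−p₂))]² / (p₂ − p₁)², with p̄ = 0.80

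This gives 334.2, so 335 per group. With the continuity correction, n/4 · [1 + √(1 + 4/(n·0.10))]² = 353.9, so 354, an exact match. Allowing for 10% loss, 354/0.9 = 393.3, so 394, rounded up in the plan to 400. Hence 400 × 0.9 = 360 evaluable per arm.

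**2. Rates implied by the quoted review figures.**

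| Source (Background section) | Calculation | Rate on treatment |
|---|---|---|
| Later review, nifedipine, on the 50% control | 0.50 × 1.50 | 75% |
| Later review, nifedipine, control solved from its own RR and absolute gain | control = 0.26/0.50 = 52%; 0.52 × 1.50 | 78% |
| Later review, α-blocker, on the 50% control | 0.50 × 1.59 | 79.5% |
| Later review, α-blocker, on a 52% control | 0.52 × 1.59 | 82.7% |
| Earlier review, either drug | 0.47 × 1.65, or 0.47 + 0.31 | 77.6% or 78% |

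The 75% is recovered. No entry reaches 85%. To reach it, the α-blocker relative risk would have to be 0.85/0.50 = 1.70 on a 50% control, 0.85/0.52 = 1.63 on 52%, or 0.85/0.47 = 1.81 on 47%.

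**3. Gap on a common control rate.**

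- 50% control: 79.5 − 75.0 = 4.5 points.
- 52% control: 82.7 − 78.0 = 4.7 points.

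**4. Power with 360 evaluable per arm** (two-sided 5%, normal approximation, no continuity correction):

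power = Φ{[(p₂ − p₁) − 1.96·√(2p̄(1−p̄)/n)] / √[(p₁(1−p₁) + p₂(1−p₂))/n]}

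| Rates | Gap | Calculation | Power |
|---|---|---|---|
| 75% v 85% | 10 | (0.100 − 1.96 × 0.02981)/0.02958 = 1.41 | 92% |
| 75% v 79.5% | 4.5 | (0.045 − 1.96 × 0.03125)/0.03120 = −0.52 | 30% |
| 78% v 82.7% | 4.7 | (0.0468 − 1.96 × 0.02962)/0.02957 = −0.38 | 35% |

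**5. The >90% statement for other comparisons.** With placebo at 50% and 360 per arm, power is above 99.9% for a single drug at 75%, and for pooled MET (720) at 75% or 80%. With pooled MET at 80% (the mean of 85% and 75%) and placebo at 70.5%, it is still 93%. At 77.0% v 70.5%, the rates in the 129-patient double-blind trial described in the Background section, power for pooled MET v placebo is 64%.

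**The case against.** The best defence is that the article only condenses the reviews. Raw arm-level rates need not equal a pooled relative risk times a pooled control rate, and the Sample size section says that information was combined, with the head-to-head trials in view. The original reviews might therefore contain an 85%. This stands in part: the documents cannot show that 85% is false, only that it cannot be rebuilt from what they quote. The head-to-head trials do not close the gap. They are cited for direction only, two of the three showed no significant difference, and no passage rate is given for any of them. The one favourable trial could mean a larger gap, but its relative reduction cannot be turned into arm rates from the figures given.

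The defence is right on four stronger readings that a reader might be tempted to adopt:

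- *Both assumed rates are unsupported.* No: 50% × 1.50 is exactly 75%.
- *The implied gap could be as small as 1.5 points (79.5% v 78%).* That sets an α-blocker rate on a 50% control against a nifedipine rate on a 52% control. On one control rate the gap is 4.5 to 4.7.
- *The 90% power claim is wrong.* It is conditional on a 10-point difference, and for that difference it is correct. The abstract claims no more, so it needs no change.
- *The >90% claim fails once placebo passage leaves 50%.* Pooled MET at 80% v placebo at 70.5% still has 93% power. The 64% arises only if the 6.5-point difference from one small trial is adopted as well. The protocol itself notes that this trial's mean stone diameter, 3.1 mm, was smaller than in all the earlier studies.

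**Conclusion.** The concern holds as a fault in the evidence claimed for one design assumption, not in the power calculation. The 85% rate is attributed to two reviews whose quoted pooled results give 79.5% (82.7% on a 52% control) for α-blockers and about 78% for either drug. The implied tamsulosin–nifedipine gap is about 4.5 to 4.7 points. At that gap, 360 evaluable per arm gives about 30% to 35% power, against about 92% at the assumed rates. A null result in this comparison would therefore not rule out a difference of the size that the quoted pooled evidence suggests.

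This rests on a two-sided 5% test, 10% loss, an unadjusted comparison of proportions, and a common control rate of 50% to 52% applied to both drugs' pooled relative risks. It is an indirect comparison across different sets of trials and not a forecast of the true difference. A 10-point target remains a legitimate choice if it is presented as one.

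**What to change.** In the Sample size section:

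1. Show how 85% was derived from the reviews. Otherwise, drop the statement that they show it and present 10 points as the chosen target difference, in line with hypothesis 2.
2. Add that with 360 evaluable per arm, power is about 30% (79.5% v 75%) to 35% (82.7% v 78%) at the gap the quoted pooled figures imply, and that a null tamsulosin–nifedipine result would not exclude a difference of that size.
3. State the rates, including placebo at about 50%, on which the >90% for other comparisons rests. The 77.0% v 70.5% case, with about 64% power for pooled MET v placebo, may be added as a sensitivity case only.

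Keep the sample size at 1,200. The cost is a few sentences of rewording. The drawback is that the stated power for the sizing comparison will look less favourable.
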